##### ***Control group***

Due to budget constraints, we are not able to provide a matched placebo as prespecified for the main study. Therefore, we will not give placebo for children in the control group, either in the mild or severe group. Children in the control group of the mild AOM group will still receive expectant observation and those in the severe AOM group will receive antibiotics, and other concomitant treatment based on physicians' preferences (if necessary). The only difference between the intervention and control group is solely whether they receive prednisolone (intervention group) or not (control group).

### **2.2.3.2 Criteria for trial drug discontinuation or modification**

When giving the prednisolone to a child, parent can mix the prednisolone powder with jelly or juice. If children vomit less than 30 minutes after having a dose of prednisolone, parents should give the same dose again. However, if they vomit again after 30 minutes, parents should not give another dose of prednisolone until the next dose on the next day. This should be noted in the symptom diary. If children keep vomiting after receiving prednisolone, parents should contact the research team. If the parents forget to give prednisolone to their children, they can give the missed dose as soon as they remember on the same day and they should also note this in the symptom diary.

If there are any adverse events and adverse drug reactions which have been assessed by research team that would require the discontinuation of drug trial and further assessment and treatment, then the treatment will be discontinued for this particular case, however follow-up will continue, where possible. This will be reported in the CRFs. Serious adverse events will be reported to Bond University's Human Research Ethics Committee (BUHREC) and the Research Committee Ethics Faculty of Medicine Universitas Indonesia (FMUI) – [name] Hospital (CMH).

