| Outcome(s)              | 
(1) Outcome Name: Recruitment rates
 Metric/method of measurement: Informed consent form and case report forms (CRFs)
 The timepoint(s) of interest: Baseline visit (visit-0)
 
(2) Outcome Name: The success of the study procedures
 Metric/method of measurement: CRFs (i.e. eligibility and randomisation form, outcomes form)
 The timepoint(s) of interest: Baseline visit (visit-0)
 
(3) Outcome Name: Ability to measure planned outcomes in main study
 Metric/method of measurement: CRFs (i.e. eligibility and randomisation form, outcomes form) and symptom diary (e.g. Visual Analogue Scale/VAS and Acute Otitis Media – Severity of Symptoms Scale/AOM-SOS), and feedback form
 The timepoint(s) of interest: Baseline visit, visit-1 (day-3 to -5), visit-2 (day-7 to -9), day3, visit-3 (day-3 to -40), and visit-4 (day-90 to -100)
 
(4) Outcome Name: Compliance to study and study drug
 Metric/method of measurement: CRF (i.e. outcomes form), the symptom diary, and number of left-over drug
 The timepoint(s) of interest: Visit-1 (day-3 to -5), visit-2 (day-7 to -9), day3, visit-3 (day-3 to -40), and visit-4 (day-90 to -100)
 
(5) Outcome Name: The verification of sample size calculation for main study
 Metric/method of measurement: CRFs (i.e. eligibility and randomisation form)
 The timepoint(s) of interest: Baseline visit (visit-0)
 |

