#### Recruitment of participants

After physicians deliver the patient information and obtain the consent from the eligible children, they will use the eligibility and randomisation form to assist them in stratifying the children based on their AOM severity. Physicians then will complete other CRFs, as the following: baseline history form and outcome form. Physician will assist the parents to complete the symptom diary. The similarity on the forms and sequences of both outcome CRF and symptom diary will help parents to be able to fill those correctly.

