### ***Allocation concealment mechanism and implementation***

The information of the eligibility and stratification which is provided by the participating physicians will help the appointed nurses to obtain the information from the randomisation website, whether the children will be allocated to the prednisolone or control group, identified by the 2-digit patient ID numbers. During the consultation, the physician will prescribe study medication for every subject with the dose based on the patient age and insert the prescription in the CRF folder. The nurse who performs the randomisation will give the prescription to the subjects who are allocated to the intervention group (prednisolone group). The subject then will give the prescription to the pharmacy, where the pharmacist will prepare the prednisolone by crushing the tablets, mixing them with sweeteners, packing the prednisolone mixed powder in a daily individual paper-pack for five days, and dispense these to the subjects along with instructions for preparation. The pharmacist will record the dispensing on the form provided by the study for this purpose.

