### **2.3.2 Blinding (masking)**

In this study, the appointed nurses and the children and their parents will know the allocation of the intervention. We will ensure that the participating physicians and the audiologists/tympanometry technicians will be blinded to the intervention allocation during the study.

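### Physician blinding is left unprotected: no step removes a control child's prednisolone prescription from the CRF folder, and drug-adherence entries are not kept off the physician's outcome form

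*Protocol*

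**What the plan says.** On masking, protocol 2.3.2 states: "We will ensure that the participating physicians and the audiologists/tympanometry technicians will be blinded to the intervention allocation during the study". The same section accepts that "the appointed nurses and the children and their parents will know the allocation of the intervention". There is no placebo (2.2.3.1, control group).

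On the prescription, 2.3.1 (allocation concealment mechanism and implementation) says of the baseline visit: "the physician will prescribe study medication for every subject with the dose based on the patient age and insert the prescription in the CRF folder". After allocation, only children assigned to prednisolone receive it from the randomising nurse. Nothing is said about the prescription of a child allocated to control.

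On the forms, the physician completes the baseline history form and the outcome form (2.1.7, recruitment of participants) and enters the tympanometry findings on the outcome form (2.2.5, participant enrolment). The WHO registration data set, outcome 4, lists as sources for compliance to study and study drug: "CRF (i.e. outcomes form), the symptom diary, and number of left-over drug". Table 1 in 2.2.5 schedules adherence to trial drug at Day 0, Day 3 and Day 7, the same visits as VAS, AOM-SOS and otoscopy.

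On the diary, 2.2.3.2 says of a vomited dose: "This should be noted in the symptom diary". Section 2.1.7 says: "Physician will assist the parents to complete the symptom diary". Section 2.2.3.3 has parents return the first two diary booklets and the left-over drug to the appointed nurse, who checks adherence; the third booklet is collected at home.

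**The concern.** Masking of the physician and the tympanometry technician is the only masking in this open-label trial. The physician performs otoscopy, interprets the tympanogram, fills in the outcome form, and chooses concomitant treatment, which 2.2.3.4 says is done without knowledge of the arm.

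Because the control arm receives nothing in place of prednisolone, any paper trace of the drug separates the arms. If such a trace lies in the folder or on the form that the physician uses at follow-up, judgements about otoscopic resolution and choices about co-treatment can be influenced by the arm. This pilot also exists to test the procedures of the main study, so a gap in its paperwork could be carried forward.

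**Working it through.** No arithmetic applies. The check follows each document from the moment it is created to the next time the physician could see it.

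**1. The prescription.** Reading 2.3.1 literally:

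| Step | Folder of a prednisolone child | Folder of a control child |
|---|---|---|
| Consultation, before randomisation | Prescription inside | Prescription inside |
| After randomisation by the nurse | Prescription handed to the family | No action stated |
| Day 3 and Day 7, if the same folder is used | Absent | Present, unless someone removed it |

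Writing the prescription reveals nothing, because every child gets one and randomisation follows the physician's baseline procedures (2.2.5). It becomes informative only after the nurse acts in one arm. Two conditions must hold for the physician to learn the arm: the control prescription stays in the folder, and the physician reopens that folder. The first follows from the text as written. The second is an assumption; the protocol does not say which folder is used at follow-up.

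**2. The outcome form.** The sections point in different directions.

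- Towards exposure: registration outcome 4 names the outcomes form as a source for drug compliance; the physician completes that form (2.1.7, 2.2.5); Table 1 places drug adherence at the outcome visits.
- Away from exposure: the outcome is a composite of taking the drug and attending visits (2.2.4.1). Section 2.4.1 takes drug completion from the diary and left-over drug. Its account of the outcome form covers pain, symptoms, otoscopy and tympanometry, not adherence. It lists dispensing and returned forms as separate CRFs.

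The outcome form may therefore supply attendance only. No section says so, and none says that drug entries are kept from the physician. The CRF layout (Appendix 3) is not shown.

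**3. The diary.** The physician's help with it is described in the recruitment section, alongside consent, stratification and the baseline forms. At that point no dose has been given. Afterwards 2.2.3.3 routes the visit booklets to the nurse, and 2.5.2 has the nurse use the diary to identify adverse effects. No section has the physician open a completed diary. This route is not supported.

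**4. How many children.** The target is 60 children allocated 1:1, so about 60 / 2 = 30 control folders. If both conditions in step 1 held throughout, a folder with the prescription would mean control and one without would mean prednisolone, so all 60 would be exposed. If either condition never held, none would be exposed by this route. The documents do not place the truth within that range.

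**The case against.** The strongest reply is that no route is shown to operate. The prescription is uninformative when written, and the protocol does not say that the physician reopens the folder. The outcome form's role in compliance can be explained by visit attendance, and the separate dispensing form and the nurse's adherence check already do much of what is wanted. The authors plainly thought about sequence: 2.5.2 lets the nurse tell the physician the allocation only after Day-3 pain has been recorded. Some key outcomes are also little exposed. The VAS pain outcome is recorded in the diary by families who know the arm by design, and static admittance is an instrument reading taken by a masked technician.

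Most of this stands. It rules out two stronger readings that a reader might infer: that assessor blinding fails through routine paperwork, and that all 60 children are affected. Both need folder handling or a form layout that the documents do not give. It also rules out inferring from 2.1.7 that the physician reads completed diaries.

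It does not remove the gap. The safeguard in 2.5.2 governs what the nurse tells the physician; it does not cover what is in the folder or on the form. The paper routes need no adverse effect to occur and could act at Day 7 as well as Day 3. Otoscopic judgement and co-treatment remain exposed even if VAS and admittance largely are not. The disclosure in 2.5.2 is a separate matter to reconcile with 2.3.2, and this point does not rest on it.

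**Conclusion.** The point holds in a limited form. Section 2.3.2 promises blinding throughout, while 2.3.1, followed literally, leaves a prednisolone prescription in control folders only, and no section states that drug-adherence entries are kept from the physician who completes the outcome form. The prescription gap follows from the text, and its effect depends on the same folder being used at follow-up. The adherence gap is a possibility that the unseen CRF layout may already close.

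The size of any bias cannot be estimated from the documents. This is an unguarded risk to the trial's only masking and an inexpensive improvement to make, not a demonstrated loss of blinding.

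**What to change.** - **2.3.1:** state that the nurse removes the prescription from every folder at randomisation, in both arms, so that all folders look the same afterwards. In the prednisolone arm it goes to the family as now; in the control arm the nurse keeps it apart from the folder.
- **Registration outcome 4 and 2.4.1:** state that drug adherence, dispensing and left-over counts are recorded only on the nurse-held dispensing and returned form, filed apart from the physician's folder, and that the outcome form carries attendance as its only compliance item.
- **Table 1:** mark the adherence row as a nurse assessment.

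The cost is a few sentences, a filing instruction and possibly a small change to form layout. No new staff are needed, because the nurse already randomises, collects the visit diaries and left-over drug, and checks adherence. The change closes the paper routes only; families who know the allocation could still mention it to the physician.

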### **2.2.3.3 Adherence monitoring**

Participating physicians will provide information regarding the administration of the prednisolone. The researcher will send a daily text-message reminder to all the parents in both prednisolone and control groups during the intervention period of five days to take the drug regularly and to complete the symptom diary daily. The text-message will also remind all the parents to visit the clinic after the 48-hour expectant observation or visit-1 (day-3), visit-2 (day-7), visit-3 (day-30), and visit-4 (day-90) for re-assessment. At each visit-1 and visit-2, the parents will return the first and second mini-booklets of symptom diary and the left-over drug to the appointed nurse (at visit-2). The nurse will then check the symptom diaries and the left-over drug for the adherence in taking intervention drugs. We will visit the patients' homes to collect the third mini booklet of symptom diary that will record the symptoms from day-7 to day-14 after the baseline visit.

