#### **2.2.3.1 Prednisolone and control group**

##### ***Prednisolone group***

Prednisolone tablets will be given in the intervention groups in both mild and severe groups. It is given at a dose of 1 mg/kg to 2 mg/kg body weight, once daily for five days. The pharmacist will crush the tablets, mix them with sweeteners, and pack them in a daily paper-pack. It should be given in a single dose at 6 to 8 am in the morning to mimic the normal diurnal rhythm of cortisol production [19,20]. Participating physicians will advise the parents to give the prednisolone at about the same time each day as a daily routine for children which will also help parents to remember.

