## 2.2.5 Participant timeline

Table 1 illustrates the timeline for visits and follow-ups. We will measure the outcomes at various time points: (1) visit-1 after the 48-hour observation (day-3); (2) visit-2 (day-7); (3) visit-3 (day-30); and (4) visit-4 (day-90). Patients will visit the hospital at visit-1 and visit-2, whilst the last two visits will be a home-visit. However, children in the mechanistic sub-study have to visit the hospitals at those follow-up visits. To improve the compliance of the study, the research personnel will send a daily text-message reminder to all the parents in the study during treatment period to take the drug, complete the symptom diary, and visit the clinic after the 48-hour expectant observation and other time points. At visit-2, parents will return the symptom diary and any left-over drug.

**Table 1.** Follow-up timeline

| TIMEPOINT                                                   | STUDY PERIOD         |                 |                           |                |                |                |
|-------------------------------------------------------------|----------------------|-----------------|---------------------------|----------------|----------------|----------------|
|                                                             | Enrolment Allocation | Post-allocation |                           |                |                | Close-out      |
|                                                             | 0 (Day-0)            | t1 (Day-3)      | Intervention ends (Day-5) | t2* (Day-7)    | t3* (Day-30)   | t4* (Day-90)   |
| ENROLMENT:                                           |                      |                 |                           |                |                |                |
| Eligibility screen                                          | X                    |                 |                           |                |                |                |
| Informed consent                                            | X                    |                 |                           |                |                |                |
| Allocation                                                  | X                    |                 |                           |                |                |                |

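### The daily reminder to take the drug goes to both arms, although control children in this open-label pilot have no study drug (minor)

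*Protocol*

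**What the plan says.** **The reminder.** Under Protocol section 2.2.3.3 (Adherence monitoring) the researcher sends a text each day to families from "both prednisolone and control groups during the intervention period of five days to take the drug regularly and to complete the symptom diary daily". Section 2.2.5 (Participant timeline) says that the research personnel "will send a daily text-message reminder to all the parents in the study during treatment period to take the drug". Neither section separates the content by arm.

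**The control arm.** The Control group part of section 2.2.3.1 says "we will not give placebo for children in the control group, either in the mild or severe group". Under section 2.2.3, mild controls have expectant observation and severe controls have an antibiotic. Section 2.2.3.1 describes prednisolone as the sole difference between the arms. Under section 2.3.1 the nurse hands the study prescription only to families allocated to prednisolone.

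**Advice on giving the drug.** The Prednisolone group part of section 2.2.3.1 says: "Participating physicians will advise the parents to give the prednisolone at about the same time each day". Section 2.2.3.3 also gives the physician the task of informing parents about administration. Sections 2.2.5 (Participant enrolment) and 2.3.1 place the physician's consultation before the nurse randomises. Section 2.3.2 requires physicians to remain blinded, while nurses and parents know the allocation.

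**The concern.** A reminder to all parents suits a placebo-controlled trial, in which every child has a study drug. The main study is planned that way and section 1.1.3 says the pilot copies its procedures, so the wording may have been carried over, although that is an inference. In the pilot, control families are told each day to give something they were never handed.

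Three things could follow. A control parent may simply be confused. A parent may look for other treatment, in an arm defined by not receiving prednisolone. Or a parent may ask the physician what the message means and so disclose the allocation to a blinded assessor. Because the pilot exists to test procedures for the main study, a procedure that does not apply to half the sample is worth correcting.

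The advice on administration raises a related difficulty. A blinded physician who speaks before allocation can only give the advice to every family, controls included. To give it to prednisolone families alone, the physician would have to know the allocation.

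**Working it through.** **1. Which drug is meant.** Section 2.2.3.3 continues with the return of left-over drug and the nurse's check of adherence to the intervention drugs. The natural reading is therefore the study drug, not an antibiotic or a symptomatic medicine.

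**2. Who has it.**

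| Group | Assigned care (section 2.2.3) | Study prescription (section 2.3.1) | Told to take the drug |
|---|---|---|---|
| Mild, prednisolone | observation plus prednisolone | yes | yes |
| Mild, control | observation | no | yes |
| Severe, prednisolone | antibiotic plus prednisolone | yes | yes |
| Severe, control | antibiotic | no | yes |

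The last two columns disagree in both control rows.

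**3. How many families.** Inputs are 60 children (section headed 2.1.6 Sample size), 1:1 allocation (section 2.1) and five days (section 2.2.3.3).

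- Controls: 60 / 2 = 30.
- Messages to controls: 30 × 5 = 150.

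This counts inapplicable messages. It does not measure bias.

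**4. Whether a stated figure changes.** The sample size section uses a standard deviation of 0.3, a difference of 0.3, a Type I error of 0.05 and power of 0.9. Taking the test as two-sided, which the protocol does not state:

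- n per arm = 2 × (1.960 + 1.282)² × (0.3 / 0.3)² = 21.0, rounded up to 22. With the t distribution the power at 22 per arm is 0.900.
- With 20% dropout: 22 / 0.8 = 27.5, rounded up to 28 per arm and 56 in total. The protocol then enrols 60.

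The planned figures reproduce, and the reminder enters none of them.

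**5. Illustration only.** The protocol gives no rate of steroid use among controls. If a share c of controls took prednisolone with full effect, the difference would fall to 0.3 × (1 − c). Power at 22 per arm (t test) would be:

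| c (assumed) | Difference | Power |
|---|---|---|
| 0 | 0.300 | 0.90 |
| 5% | 0.285 | 0.87 |
| 10% | 0.270 | 0.83 |
| 20% | 0.240 | 0.74 |

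Nothing in the protocol ties the reminder to any of these values of c.

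**6. The advice on administration.** The order is physician consultation, randomisation by the nurse, then dispensing by the pharmacist, who already gives preparation instructions (section 2.3.1). No section says when the physician gives the advice. Sections 2.2.3.1 and 2.2.3.3 do not explain how it reaches prednisolone families without either reaching controls or requiring the physician to know the allocation.

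**The case against.** **The wording may be shorthand.** The protocol describes what the reminder is for and does not reproduce the message. A single list of drug, diary and visits could mean whatever applies to each family. Against this, section 2.2.3.3 names both groups explicitly and section 2.2.5 repeats the instruction, so staff following the text would send the drug line to everyone. Daily contact in both arms is a strength, because it balances attention and diary prompting, and it should stay.

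**Contamination.** A reader might infer that the text contaminates the control arm. The document does not support that. Parents know the allocation (section 2.3.2), only prednisolone families get a prescription, the pharmacist records dispensing, and a text supplies no drug. A residual route exists: section 2.2.1 reports that enough surveyed physicians would prescribe corticosteroids for this condition, controls may have other treatment at the physician's discretion, and the exclusion criteria cover only earlier steroid use. That makes contamination possible but does not demonstrate it.

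**Unblinding.** Parents who know the allocation meet blinded physicians at the follow-up visits in any case. Section 2.5.2 also has the nurse report the allocation along with any adverse effects, once the day-3 outcome is recorded. The text may prompt a revealing question, but the exposure comes mainly from the open-label design.

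**Effect by stratum.** It is tempting to say that about 19 or 20 of the 30 controls are mild (0.65 × 30 = 19.5). The 35% severe share is an assumption for the main study that the pilot is meant to check, and the pilot recruits only through specialists at tertiary centres, so the split is not established here. Nor must severe controls read the drug as their antibiotic: symptomatic medicines are also allowed, and children in both severe arms take antibiotics.

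**The advice.** Giving every parent the same information before randomisation is compatible with a blinded physician, and the pharmacist's instructions already cover preparation. This is why it is a secondary point.

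**Conclusion.** The inconsistency stands and is minor. As written, the drug line of the reminder is wrong for about 30 of 60 families, given 1:1 allocation and full recruitment, and assuming the message follows the stated purpose literally. The consequence is a modest risk of confusion, treatment-seeking or questions to the blinded physician, and the protocol gives no basis for putting a number on it. The sample sizes of 22 per arm, 56 and 60 are unaffected, and the comparator remains defined as no prednisolone. The assignment of administration advice to blinded physicians before allocation is a lesser matter of reconciling sections.

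**What to change.** - **Sections 2.2.3.3 and 2.2.5:** use two message templates. Diary and visit reminders stay identical, with the same daily frequency, in both arms. The study-drug line goes to the prednisolone arm only.
- **Sender:** state that the person sending the texts holds the allocation list and does not assess outcomes. Section 2.3.2 lists the researcher neither as blinded nor as aware of the allocation, so one sentence there would settle it.
- **Sections 2.2.3.1 and 2.2.3.3 against 2.2.5, 2.3.1 and 2.3.2:** reconcile who advises parents on giving prednisolone, and when. One option is for the unblinded nurse or the pharmacist to do so after allocation.

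The cost is a second text template, an allocation list for the sender and small wording changes. No change to sample size, visits or outcomes is needed.
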